#### Control

All participants receive treatment as usual (which will be recorded for both groups) however, in addition, the control group will receive an advice booklet about exercise after stroke, based on a Stroke Association's publication.^24^ This offers a low-cost alternative to ReTrain that might be provided to stroke survivors, although it does not give advice on specific exercises. We believe offering an advice booklet to the control patients, will improve recruitment and retention.

#### Assessment and outcomes

##### Initial screening assessment

Those expressing an interest in taking part in the study will be contacted by telephone by a member of the research team and, with their permission, be asked questions to assess their eligibility. These will address: diagnosis of stroke, time since stroke, status regarding receipt of poststroke physical rehabilitation, mobility, potential contraindications to exercise and willingness to exercise regularly as part of intervention but also willingness to be in the control group. Permission will be sought to contact the person's GP (and/or referring clinician, if this is the recruitment route) to obtain relevant medical history and screen for contraindications. This verbal consent will be documented. A medical screening questionnaire will be sent to the GP if the person appears eligible for inclusion in the study. The research team will await receipt of the completed GP letter but will contact the practice after 7 days if there has been no reply from the GP. Once the GP letter has been received by the research team, those potentially eligible will be contacted to arrange a home-based visit. Those not eligible will be thanked and informed of the ineligibility.

##### Home-based screening and data collection

Those apparently eligible for inclusion will be visited at home by a member of the research team to provide further information about the intervention and study, and to obtain written consent. There are discrete activities within the trial that require specific consent from the participant. As part of the consent process participants will be asked whether they would be willing for a researcher to look at their medical records to view the number of primary and secondary care resources they used over the course of the trial. They will also be asked whether they would like to take part in an interview at the end of the trial to discuss their experiences. Participants will also be asked whether they would be happy to be video-recorded during some training sessions, should they be allocated to the ReTrain programme. All participants will be asked their consent again immediately prior to these activities so that they can confirm or decline consent.

Demographic and other personal information will also be collected at this time:
Date of birth, gender;Stroke history (type, severity, date, summary of rehabilitation);mRS score, established by a simple questionnaire;^29^Medical history (comorbidities, current treatments);Social history (employment status, previous employment);Physical exercise history (prestroke, poststroke, last month: type, frequency, intensity).

Depending on recruitment patterns, those eligible and consenting may be required to wait several weeks before start of the intervention. They will be kept informed of timings by a member of the research team.

##### Clinical outcomes

We will collect both the objective physical outcome and participant-reported outcome measures (PROMs) that we intend to collect in a definitive trial. Outcome selection was informed by discussions with our SUG and data from our preliminary studies. The measures are: the Rivermead Mobility Index;^37^
^38^ the Timed Up and Go Test;^39^ a modified Patient-Specific Functional Scale;^40^ 7-day accelerometry^41^ (using the GENEActiv which is waterproof, can be continuously worn and programmed to start and stop automatically, see http://www.geneactiv.co.uk); the Stroke Self-efficacy Questionnaire,^42^ physical exercise levels assessed by physical activity diary, the Fatigue Assessment Scale,^43^
^44^ exercise beliefs and exercise self-efficacy questionnaires,^45^ the SF-12,^46^ the EQ-5D-5L^47^ and Stroke Quality of Life questionnaires^48^
^49^ and the Carer Burden Index.^50^ Health and social service use will be measured through a Service Receipt Inventory.^51^ The PROMs and instructions for their completion will be collated into a booklet.

Baseline assessments will be done by a member of the research team. Physical outcome follow-up assessments (at 6 and 9 months) will be conducted at the participant's home, by a blinded assessor trained in all elements of the assessment procedure. Self-report questionnaires for 6-month and 9-month follow-ups will be compiled into a single booklet with instructions for completion, and mailed to participants along with the accelerometer and a physical activity diary, a week before the home visit, unless participants request a visit from a member of the research team to help fit the accelerometer. If materials are posted, prior to each blinded assessor visit a member of the research team will call the participant to check that they are still available to meet. During this call the member of the research team will check how the participant is progressing with the questionnaire and check whether the accelerometer is still being worn and is comfortable. Participants will also be asked to report any adverse events, enquiring explicitly about whether they have experienced any fatigue, muscle soreness or falls (all expected adverse events). If materials are delivered by a member of the research team, the accelerometer will be fitted, adverse event report taken and questionnaire booklets left for completion. The blinded assessor will check questionnaires for completeness and understanding during their visit. Table 1 indicates the outcome instruments and the time points for their use.

**Table 1 BMJOPEN2016012375TB1:** Trial outcome measures and when used (1=baseline; 2=postintervention; 3=follow-up)

Measure	Time to administer	Assessment		
	(mins)	1	2	3
*Primary*				
Rivermead Mobility index^37^ ^38^ 15-item, dichotomously scored measure of mobility disability. 14 items are self-report and 1 (standing for 10 s without aids) is scored by observation.	5	✓	✓	✓
Timed Up and Go Test^39^ Objective measure of mobility, balance and locomotor performance, in which the individual is observed and timed rising from a chair, walking 3 m, turning and returning to the chair	5	✓	✓	✓
Modified Patient Specific Functional Scale^40^* Identification by individual of up to 5 functional tasks that are important and difficult to perform, and rating of ability to perform each task on a 0–10 scale	10	✓	✓	✓
Physical Activity Diary* Participants record the type of activity and its duration each day of the week (1–2 min/day to complete)	10–15	✓	✓	✓
Physical activity—7-day accelerometry^41^ Worn by individual to assess physical activity behaviour over 7 days. Should take 5 min to fit watch and 10 min to post back	15	✓	✓	✓
*Secondary*				
Fatigue Assessment Scale^43^ ^44^* 10-item self-completion questionnaire in which aspects of fatigue are rated on how regularly they are experienced, using a 5-point scale	5	✓	✓	✓
Stroke Self-efficacy Questionnaire^42^* 10-item questionnaire in which participants rate their confidence in completing some tasks that may have been difficult for them since their stroke	5	✓		✓
Exercise beliefs questionnaire^45^* Measures attitudes to exercise by rating levels of agreement to 5 statements about what it can achieve for the individual	3	✓		✓
Exercise self-efficacy questionnaire^45^* Self-rating of confidence to overcome 4 personal barriers to exercise	3	✓		✓
Stroke Quality of Life^48^ ^49^* Self-rating of 12 dimensions of lifestyle and personal functioning	5	✓		✓
EQ-5D-5L^47^* Measuring health-related quality of life and can be used for cost-utility analysis	3	✓		✓
SF-12^46^* Abbreviated version of the Short-Form-36 self-completion questionnaire measuring health-related quality of life. It can also be used to calculate the SF-6D, which may be used for cost-utility analysis	5	✓		✓
Service Receipt Inventory^51^* Record of types and amount of use of health and social care resources including medication, clinical contacts, formal and informal social care. Completed by assessor drawing on participant and family accounts, and clinical records if available	10	✓		✓
Carer Burden Index^50^* Carers of stroke survivors rate the difficulties and challenges of providing care	5	✓		✓
Adverse incidents^52^	3		✓	✓

*Questionnaire may be mailed for self-completion before home visit or left after a research team visit.

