^33^ ReTrain is predominantly based in a community centre with twice weekly, 90 min sessions over 3 months, comprising: (1) an introductory one-to-one session (as a home visit); (2) group classes with up to two trainers and eight clients (preserving the maximum ratio of one trainer to four participants); (3) a closing one-to-one session (as a home visit). This is followed by three drop-in sessions over the subsequent 3 months at the community centre. The final one-to-one session and monthly drop-in sessions address concerns raised by our preliminary study participants of the sudden cessation of support.^23^ A more thorough description of the intervention can be seen in figure 2. The ReTrain Trainer and Intervention Delivery manuals were designed using an overarching theoretical framework that enabled existing evidence-based components (from the physiology of exercise training, Behaviour Change Techniques^34^ and stroke rehabilitation guidelines) to be mapped together with the as yet unresearched ARNI principles and techniques. The theoretical framework is known as the Information-Motivation-Behavioural Skills model^35^ and enables intervention mapping to take place.^36^ This mapping process will be developed and refined as part of the feasibility work of this study and will specify the essential resources, activities and behaviours of trainers and clients that must be present in sessions and across the programme. Session checklists will capture the main content and indicate where flexibility is permitted (for individualisation of training) and allow evaluation of intervention fidelity.

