##### Adverse events

In preliminary studies, several falls were recorded, though none required medical intervention. Transitory muscle soreness and high levels of postexercise fatigue were also reported in some cases, but there appears to be a low risk of serious adverse advents associated with this intervention. Those providing the intervention are trained in health and safety procedures and will be required to ask participants about any adverse events occurring at home, and record any reported or witnessed during the intervention. Participants will also be asked about adverse events as part of the process evaluation (to maintain blinding of the outcomes assessor). Any serious adverse event will be immediately reported to the trial sponsor and relevant ethics committee if the chief investigator (CI) deems it related to the intervention, and to the independent Trial Steering Committee (TSC) members who are also acting as our Data Monitoring and Ethics Committee.

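### The questionnaire check, and possibly the Service Receipt Inventory, give the blinded assessor an avoidable route to learning the allocation

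*Protocol article*

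**What the plan says.** Under Clinical outcomes, a blinded assessor takes the follow-up physical measures at the participant's home and has a second task: "The blinded assessor will check questionnaires for completeness and understanding during their visit". The self-report booklet is "mailed to participants along with the accelerometer and a physical activity diary, a week before the home visit".

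Table 1 describes the diary: "Participants record the type of activity and its duration each day of the week". The diary carries an asterisk, whose footnote reads: "Questionnaire may be mailed for self-completion before home visit or left after a research team visit".

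The Service Receipt Inventory carries the same asterisk, but its own row says: "Completed by assessor drawing on participant and family accounts, and clinical records if available". The row gives its content as: "Record of types and amount of use of health and social care resources including medication, clinical contacts, formal and informal social care". It is ticked at baseline and at the last follow-up, not at 6 months.

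The Blinding section sets general safeguards. Participants are told to conceal their arm, unblinding incidents are logged, the assessor guesses the allocation once the assessments are done, and the assessor is based away from the research centre. It also says that researchers on the process and economic evaluations cannot be blinded. The Adverse events section adds a specific safeguard: "Participants will also be asked about adverse events as part of the process evaluation (to maintain blinding of the outcomes assessor". The first study objective under Aims includes testing the blinding of outcome assessment.

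**The concern.** The plan recognises that talking with a participant about what has happened since randomisation can unblind the assessor, and it moves adverse-event questions elsewhere for that reason. It describes no equivalent step for the diary or the Inventory. Checking that a form has been understood means discussing the answers, not only looking for blanks. The section on feasibility, acceptability and process outcomes lists exercise diaries among the measures of intervention fidelity, so the plan itself treats diary content as informative about ReTrain. Family members, whose accounts feed the Inventory, may have driven the participant to the training venue (Foreseen difficulties).

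Two things are at stake. The Timed Up and Go could be scored by someone who has just learned the arm. And the pilot's evidence on whether blinding is workable could be coloured by a paperwork step that the definitive trial need not have.

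**Working it through.** The plan gives no figure to reproduce. The check sets its statements side by side, with simple counts.

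**1. What the assessor may see**
- *Diary.* Table 1's footnote treats it as a questionnaire. The Clinical outcomes text names it separately from the booklet. That the assessor's check covers it is therefore an inference, though a reasonable one.
- *Inventory.* The row says an assessor completes it; the footnote allows self-completion. The row does not say which assessor, and at baseline a research-team member does the assessments. At follow-up, the Blinding, Clinical outcomes and Adverse events sections use the word for the blinded assessor, so that is the natural reading at 9 months, but it is not explicit.
- *Other asterisked forms.* These rate fatigue, confidence, beliefs, function, quality of life and carer burden. None records training.

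**2. What a diary week could contain**
- The Abstract gives 25 sessions. Less 2 home visits, 25 − 2 = 23, which matches the 23 venue sessions under Foreseen difficulties. Less 3 drop-ins, 23 − 3 = 20 group classes. At two a week, 20 / 2 = 10 weeks, which fits "twice weekly, 90 min sessions over 3 months".
- The drop-ins are monthly over the next 3 months, so they run to about month 6 of the programme.
- Assume follow-up is counted from programme start (the article does not state the origin). A one-week diary at 6 months then catches at most one drop-in, and one at 9 months catches no scheduled session.
- If follow-up is counted from randomisation and training began *w* months later, the visits fall at programme months 6 − *w* and 9 − *w*. For any *w* below 3, the first is still after month 3 (drop-ins, not classes) and the second still after month 6 (no sessions).
- The diary would therefore mostly show independent exercise. ReTrain aims to establish a regular home programme, so this hints at the arm without stating it.

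**3. How many visits**
- Questionnaire check: 48 participants × 2 follow-ups = 96 visits at most.
- Inventory: 48 × 1 = 48 at most.
- At the 20% attrition predicted under Sample size, and if all of it came before the visit, 48 × 0.80 = 38.4, or about 38 per time point.
- The article gives nothing from which to derive how often a form would reveal the arm.

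**4. What one guess can show**
A correct guess at the end of the visit may come from the paperwork or from anything else, such as a remark or how the participant moves. One recorded guess cannot divide the two. A guess before the paperwork and another after it can, because a change between them points to the paperwork.

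**5. Which outcomes are exposed**
The Timed Up and Go is observed and timed. Of the 15 Rivermead items, 14 are self-report and 1 is observed. Both instruments are listed as primary in Table 1.

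**The case against.** The strongest reply is that the plan already takes blinding seriously and the leak is small. Participants are asked to conceal their arm, incidents are logged and a guess is recorded. Diary weeks fall largely after the classes. People already committed to exercise may enter either arm (Participant recruitment) and controls receive an exercise booklet, so reported exercise separates the arms poorly. The order of the visit may sit in the assessment standard operating procedure that Trial monitoring and management says will be written. A pilot that found a step to be unblinding would have produced a useful result.

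Much of this stands. The absence of a visit order from a condensed article is not itself a fault. Incident logging would also help in interpreting the guesses. But the point rests on tasks that the article does assign, and the safeguards discourage or record unblinding without removing this source of it.

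Stronger readings are tempting, and the document does not support them:
- *The blinded assessor must complete the Inventory.* The row does not name the blinded assessor, and the footnote allows another mode.
- *The forms record what training was done.* Only the diary records activity. The Inventory lists health and social care, not training.
- *The paperwork exposes allocation.* It may reveal it, through a drop-in near month 6, a home programme or a family remark. Nothing shows that it usually would.

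**Conclusion.** The point holds as an avoidable risk of unblinding, not as a demonstrated failure of blinding. The questionnaire check creates the risk at both follow-ups (up to 96 visits). The Inventory, if the blinded assessor completes it, adds to it at 9 months only (up to 48). No rate of disclosure, and so no size of bias, can be given. The outcomes open to influence are chiefly the Timed Up and Go and one Rivermead item. The effect on objective 1 is more direct, because a single end-of-visit guess mixes paperwork with every other cause.

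This rests on three assumptions: that the check extends to the diary, as the footnote suggests; that the assessor in the Inventory row is the blinded one at 9 months; and that the paperwork comes before the guess. If the first two are false, the remaining risk is conversation over the other questionnaires, which is smaller. The conflict between the Inventory row and its footnote stands in any case.

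**What to change.** 1. At each follow-up visit, score the Timed Up and Go and the Rivermead first, then record the assessor's allocation guess, and only then check the questionnaires. Keep the incident log and record a second guess at the end of the visit, so that later unblinding is still captured.
2. Have the diary returned sealed to the research team, for example with the accelerometer, which is already posted back. The assessor then does not check it.
3. Reconcile the Inventory row with its footnote: one mode for all participants, handled by research-team staff who are already unblinded.

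The cost is small: edits to Table 1, to the Clinical outcomes and Blinding text and to the assessment procedure, using staff who already contact participants before the visit. The downside is that unblinded staff would check the completeness of the Inventory and of the diary, which Table 1 lists as primary, and that diary gaps would come to light only after the visit.

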##### Feasibility, acceptability and process outcomes

The feasibility of a definitive RCT will be determined by collecting and analysing the following pilot study data. The numbers and details of those approached; the recruitment and retention rates, as well as recruitment patterns from each route and geographical area. Those who decline to participate or drop-out of the study will be invited to participate in a brief phone interview regarding their reasons. Acceptability of randomisation, outcome measurement burden, interventions and other aspects of trial participation will be investigated by checking completion of questionnaires and objective assessments as well as through interviews with 10 intervention and 10 control group members (purposively selected to ensure inclusion of different genders, ages, disability levels and previous exercise experience) and by postintervention interviews with the trainers. These qualitative interviews will use a semistructured interview schedule designed to cover the above issues as well as ask about other personal and contextual factors that may affect participation and outcomes (ie, barriers and facilitators) including what refinements might be needed for the definitive trial delivery. Interviews will be conducted by a member of the research team at a convenient time and location for the participant after the intervention period. Adverse events will be identified,^52^ via trainer reports and the research staff explicitly questioning participants, using trial standard operating procedures. No serious adverse events were reported in the preliminary studies. Intervention fidelity will be assessed by several methods: attendance, accelerometry, exercise diaries, session checklists and video analysis of selected training sessions in each programme.

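### Adverse-event enquiry is more frequent in the ReTrain arm and rests on participant report and trainer observation, with no stated check against the health-care contacts the trial also records

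*Protocol article*

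**What the plan says.** The protocol article describes the adverse-event routes in three places.

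- *Feasibility, acceptability and process outcomes*: events are identified "via trainer reports and the research staff explicitly questioning participants, using trial standard operating procedures".
- *Clinical outcomes*: for people who receive the booklet by mail, the rule is that "prior to each blinded assessor visit a member of the research team will call the participant to check that they are still available to meet". At that call, or at the delivery visit that replaces it, "Participants will also be asked to report any adverse events, enquiring explicitly about whether they have experienced any fatigue, muscle soreness or falls". Table 1 accordingly lists adverse incidents at the postintervention and follow-up assessments.
- *Adverse events*: those delivering the training "will be required to ask participants about any adverse events occurring at home, and record any reported or witnessed during the intervention". Participants are also asked within the process evaluation, so that the outcome assessor stays blinded.

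Health-care use is recorded separately. Table 1 defines the Service Receipt Inventory as a "Record of types and amount of use of health and social care resources including medication, clinical contacts, formal and informal social care", taken at baseline and 9 months. Under *Home-based screening and data collection*, participants are asked to let a researcher "look at their medical records to view the number of primary and secondary care resources they used over the course of the trial". *Data analysis* plans to match the Inventory with medical records in a subgroup, to see whether resource categories are misunderstood.

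People who decline or "drop-out of the study will be invited to participate in a brief phone interview regarding their reasons". *Trial monitoring and management* announces a standard operating procedure (SOP) on adverse incidents. It is not among the documents at hand.

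**The concern.** Every named route depends on what a participant reports or a trainer sees, and the trainer route exists in one arm only. Someone who has died, is in hospital or has stopped responding cannot answer a pre-visit call. An admission or a new stroke has no prompt of its own, so it depends on the participant mentioning it in reply to a general question. The trial meanwhile plans to collect information on the same contacts for another purpose.

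Two things are at stake. First, the two arms' event counts would come from different intensities of enquiry, so a difference or a similarity between them would be hard to read. Second, objective 4 includes confirming that safety data can be collected. A pilot that holds an independent source but does not compare it with the event log cannot say how complete that log is.

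**Working it through.** No stated figure lies behind this point, so the check is mainly a comparison of the text.

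**1. Routes by arm**

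| Route | ReTrain | Control |
|---|---|---|
| Trainer enquiry and observation | Up to 25 sessions (Abstract) | None |
| Staff contact before 6-month visit | 1 | 1 |
| Staff contact before 9-month visit | 1 | 1 |
| Process evaluation | Yes, number not stated | Yes, number not stated |

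Leaving the process evaluation aside, controls have 2 scheduled enquiries and ReTrain participants have 2 plus up to 25. The 25 is an upper bound, because the article does not say that trainers ask at every session. Training runs for 3 months, with three drop-in sessions over the next 3, so the imbalance falls in the first 6 months. From 6 to 9 months the scheduled staff enquiry is the same in both arms.

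**2. Recall periods in controls**

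The first contact looks back about 6 months and the second about 9 − 6 = 3 months. One recall contact therefore covers about 6/9, or two thirds, of control follow-up.

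**3. Stated purposes of the health-care data**

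- Inventory: resource use, and a record of usual care in both arms (*Usual care*).
- Notes review: the amount of primary and secondary care used. The consent described under *Trial monitoring and management* has the same purpose.
- Inventory-to-records match: whether Inventory categories are understood, in a subgroup.

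None of these passages gives the data a safety role, and none rules one out. Table 1 has the assessor complete the Inventory (it is also marked as one that may be posted for self-completion), while *Adverse events* keeps adverse-event questioning away from the assessor. The person likely to see an admission in the Inventory is thus outside the adverse-event route, and no hand-over is described.

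**4. People who leave follow-up (illustration only)**

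Inputs from *Sample size*: 48 participants and predicted attrition of 20%. 48 × 0.20 = 9.6, so about 10 people, or about 5 per arm, would be beyond routine staff questioning by the end.

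The document gives no serious-event risk. With an assumed risk p in each of these 10 people, the chance of at least one serious event among them is 1 − (1 − p)^10:

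| Assumed p | Expected events (10p) | Chance of at least one |
|---|---|---|
| 2% | 0.2 | 18% |
| 5% | 0.5 | 40% |
| 10% | 1.0 | 65% |
| 20% | 2.0 | 89% |

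This is the chance that an event occurs in the group, not that it is missed. A trainer or the drop-out call might still pick it up.

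**The case against.** The strongest reply is that this is a condensed article which defers to SOPs, one of them specifically on adverse incidents. Whether an admission found in the notes is entered in the event log is the kind of detail such an SOP holds. That stands. A reader might infer that service-use data never reach the safety record, or that an admission would be costed but never treated as a serious event. The text supports only the absence of a stated link.

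Other parts of the reply also stand:

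- Participants are asked about any adverse event, so the three prompts are additions to an open question. The falls prompt may also bring out some fractures.
- Enquiry can be by telephone, so it does not require a visit.
- Trainers question ReTrain participants during the programme, so long recall is mainly a control-arm problem.
- A call about reasons for leaving may well reveal an event that caused the departure.
- The health-care data are an imperfect standard. The only post-baseline Inventory is at 9 months and rests on participant and family accounts, with clinical records if available. People who leave earlier miss it. Matching covers a subgroup, and consent is confirmed again before notes review.

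It might also be inferred that the case for having no separate monitoring committee falls. It does not follow: the low-risk statement rests on the preliminary studies, not on this trial's event count.

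The reply does not remove the unequal enquiry. The article states the sources and the prompts, and one source exists in one arm only. An unseen SOP might add a cross-check, but it would not by itself widen a consent described for resource use.

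**Conclusion.** The point holds in a limited form and is worth correcting. As written, enquiry about adverse events is unequal between arms (two scheduled staff contacts in controls, against the same two plus up to 25 trainer sessions) and depends on self-report outside those sessions. No stated step checks it against the health-care contacts the trial records. Under-counting of serious events is possible in both arms and is probably greater in controls and among the roughly 10 people expected to leave follow-up.

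The direction rests on the assumption that more frequent asking finds more events. The number missed cannot be derived from the document, since it gives neither event rates nor recall loss, and the conclusion does not depend on the illustrative risks above. If the adverse-incident SOP already contains a cross-check applied alike in both arms, the records part reduces to stating it in the protocol. The prompts and the drop-out questions would still need attention.

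**What to change.** 1. In *Clinical outcomes*, add hospital admission or emergency attendance, new stroke and fracture to the explicit prompts at the pre-visit contact, worded identically in both arms.
2. In *Feasibility, acceptability and process outcomes*, ask the same questions in the drop-out phone interview.
3. In the same section and in *Adverse events*, name the Inventory and, where consent allows, the notes review as further sources in both arms. Unblinded research staff, not the assessor, should compare each admission, emergency attendance or death found there with the event log and enter any unmatched one for assessment.
4. Report by arm how many serious events were found only by this reconciliation. That gives objective 4 a direct measure.

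**Cost:** three extra prompts and a few hours of matching on data already planned. The notes part needs a consent-wording amendment with sponsor, Research Ethics Committee and R&D approval. Because recruitment has started, it may also need renewed agreement from those already enrolled; the consent already sought just before notes review offers a place for it. The reported event count may rise. The check remains partial unless the notes review extends beyond the planned subgroup, and the report should say so.
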